**Domain 5 - treatment correlates** To measure stigma-related concerns associated with receiving treatment for depression, participants complete the Stigma Checklist Questionnaire [62], a measure specifically designed for use with low-income Spanish-speaking or bilingual Latino patients. The questionnaire consists of 7 items designed to identify participants’ perceptions of others who have depression and take medication, as well as their fear of relatives learning that they are dealing with depression. The reliability of the scale has been reported at a Cronbach’s alpha of 0.69.

The Therapeutic Alliance with Clinician Questionnaire [63] assesses the strength of the therapeutic relationship using a 9-item Likert scale format. The Spanish version of the questionnaire [64] was evaluated with a sample predominantly comprised of depressed individuals and achieved high internal consistency (*α* = 0.96) and an item component correlation of 0.70. The authors concluded that the measure has both clinical and research utility.

To elicit feedback about both treatment conditions, we administer an in-house developed questionnaire every other session. Participants rate the treatments on a 0 to 5 Likert-type scale across 10 items including “to what extent do you believe that this treatment has improved your depression/low mood?”, and “how valuable do you think this treatment would be for individuals who experience depressed/low mood?” This treatment satisfaction scale ranges from 0 to 50, with higher scores representing higher satisfaction.

### Protection of participants

Given that a diagnosis of MDD is a criterion for eligibility, participants’ safety and privacy throughout the course of the study is a priority. Accordingly, we have incorporated a Data Safety Monitoring Board (DSMB) and a detailed safety protocol. The DSMB was created to monitor and ensure participants’ safety through the course of treatment. Members of the DSMB include five independent researchers who have extensive experience in treatment research with BATD and depression treatment research in general. These individuals are involved in the project as DSMB members in order to guarantee objectivity regarding participants’ safety, study conduct, and recommendations concerning the continuation or modification of the project’s safety protocol. These members participate in an annual teleconference to conduct continuous evaluation of the clients’ safety protocol. In addition, monthly reports regarding clients’ progress in both treatment conditions are generated. Any potential issues that pose risk to participants (during screening or during the study course) are discussed over the telephone with the DSMB.

For immediate crisis intervention, we developed a thorough safety protocol. Every research assistant and therapist involved in the study is trained in these procedures following already established protocols for depression treatment development projects conducted at the laboratory. In the case that a participant reports suicidal intent and a plan, research assistants administer the MSSI [57]. Prior to administering the MSSI, the research assistant notifies the authors involved in the study. Immediately after conducting the MSSI, the research assistant informs the participant’s therapist of the results. The therapist engages in an honest discussion with the participant about his or her likelihood of carrying out suicide. The therapist conducts a lethality risk assessment and draws a contract with the participant indicating that he or she will not make any attempts to carry out the plans. The therapist and research assistant document the outcome of the discussion and their impressions. The appropriate authorities are notified if the participant is perceived to be in imminent danger (in or out of session).

Within 24 hours of conducting a safety protocol, a conference call discussing relevant details takes place with all of the DSMB members. The goal of this discussion is for DSMB members to provide a future plan to ensure the participant’s safety. A similar protocol is followed in the case that a participant reports suicidal ideation to his or her therapist. In that case, the MSSI is not administered; rather a lethality risk assessment is given primary emphasis. All other procedures are then followed as described above.

### Sample size considerations

We based our sample size needs on effects observed in the literature, including other treatment studies, and by making informed decisions about the magnitude of effects of BATD in this population that would likely be of clinical significance. For the primary hypothesis that BATD would result in greater reductions in depressive symptoms, we calculated the sample size required based on a recent meta-analysis conducted that examined the effect size of BA relative to control conditions [29] and on a treatment study that compared cognitive behavioral therapy to an active treatment condition (interpersonal psychotherapy) conducted by Rosselló and colleagues [65] in a Spanish-speaking Latino sample. These studies yielded effect sizes of 0.43 and 0.74, respectively, indicating medium to large effects. Our proposed sample size of 30 in each cell fits well within that suggested by a power analysis using these two reported effect sizes to allow for a power of 0.80 using an alpha of 0.05 [66]. Our sample size also follows recommendations of including 15 to 30 subjects per cell in this stage of treatment development [67].

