## Methods/design

### Design

Sixty depressed Latinos with LEP from the community will be randomized to receive individual BATD (*n* = 30) or an individual contact time-matched SC condition (*n* = 30). The design allows for the examination of treatment group differences in depression, activity level and contact with environmental reinforcement, treatment adherence, treatment satisfaction, therapeutic alliance, and perceived stigma between conditions, consistent with our three study aims. Assessments take place immediately prior to each session and at 1-month post-treatment. This study was approved by the University of Maryland-College Park’s Institutional Review Board (protocol no. 403879–2). We requested to obtain participants’ verbal informed consent and not written informed consent to protect the privacy and confidentiality of a sample that may be represented predominantly by immigrant Latinos, who may not be in the US on legal terms.

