## Discussion

The current study is an RCT of 60 depressed Latinos with LEP in the community randomized to BATD (*n* = 30) or to SC (*n* = 30). Strengths of the trial involve a contact time-matched control and the utilization of MDD as inclusion criteria rather than elevated depressive symptomatology. Another important aspect of the study is that, in comparison to other treatment trials among Latinos, the current study is utilizing a direct, Spanish translation of the BATD manual without *a priori* cultural modifications. Similar to the open-label trial, we made this decision because BATD facilitates treatment customization for each client. Therefore, throughout treatment, the therapist emphasizes only values that are important to the client without prior assumptions about their culture.

We also foresee specific study limitations. First, given that the current study is being conducted as part of a small, pre-doctoral grant, funds are limited for recruitment in mass media, limiting the reach of our efforts. In addition, we may observe a high dropout rate in this study, consistent with trends in treatment development studies with this population [16,17]. Given that our sample is already small, small but significant differences between the treatments may go undetected (type II error). However, this concern is mitigated given the important information that may be gained through the study, including the efficacy of the two therapies tested, the proposed mechanisms of change, and the treatment correlates examined. Another limitation is the high rates of comorbid psychopathology we may observe in our sample. This would be consistent with previous literature in this particular population and our observations from the BATD open-label trial. Although we believe that this fosters external validity of our results in the context of an RCT, it may also result in decreased overall treatment gains [69].

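### The sample-size statement is wrong as written: 30 per arm supports 80% power only at the larger planning effect (0.74), and a two-sample t-test at the smaller one (0.43) has power of about 0.37

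*Protocol article*

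**What the plan says.** The section Sample size considerations ties the calculation to the main efficacy question: "For the primary hypothesis that BATD would result in greater reductions in depressive symptoms, we calculated the sample size required". It draws on a meta-analysis of behavioral activation against control conditions and on a trial of cognitive behavioral therapy against interpersonal psychotherapy in a Spanish-speaking Latino sample. Of these it says: "These studies yielded effect sizes of 0.43 and 0.74, respectively, indicating medium to large effects". It then concludes: "Our proposed sample size of 30 in each cell fits well within that suggested by a power analysis using these two reported effect sizes", the target being "to allow for a power of 0.80 using an alpha of 0.05". As a second, separate basis it cites a recommendation of 15 to 30 subjects per cell at this stage of treatment development.

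The section names no test, sidedness, correlation between repeated measures, effect trajectory or dropout allowance. The Discussion warns that "we may observe a high dropout rate in this study, consistent with trends in treatment development studies with this population" and that, because the sample is already small, "small but significant differences between the treatments may go undetected (type II error".

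**The concern.** One sample size, one power and one alpha are set against two effects that differ by a factor of about 1.7 (0.74 / 0.43). Required sample size varies with the inverse square of the effect, so the two requirements should differ about threefold ((0.74 / 0.43)² = 2.96). A single figure of 30 per arm cannot sit comfortably with both.

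The effect at which the statement fails is also the one closer to this trial's question. The 0.43 comes from behavioral activation against control conditions, whereas neither arm of the comparison behind 0.74 is described as behavioral activation.

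At stake is how the result is read. Someone who relies on 80% power could take a non-significant difference as evidence that the treatment adds nothing to supportive counseling. With a simple two-group test, the trial would have had little better than a one-in-three chance of detecting its own effect for behavioral activation.

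**Working it through.** **Inputs.** From Design and Sample size considerations: 30 per arm, 1:1; alpha 0.05; target power 0.80; effects 0.43 and 0.74. Assumptions made here: the effects are standardised mean differences d (this fits the article's description of them as medium to large), and the test is a two-sample t-test, two-sided unless noted.

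**Formula.** With n per arm, the noncentrality is d × √(n/2) on 2n − 2 degrees of freedom. Power is the probability that the noncentral t exceeds the critical value.

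**The plan's figure, at 0.74.** Noncentrality = 0.74 × √15 = 2.87. Power = 0.805. Required n = 29.7, so 30 per arm. The stated 0.80 is reproduced, with less than one participant per arm to spare.

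**The same calculation at 0.43.** Noncentrality = 0.43 × √15 = 1.67. Power = 0.374. Required n = 85.9, so 86 per arm. The stated 0.80 is not reproduced.

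**Other readings.**

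| Reading | Effect | Power at 30 per arm | n per arm for 0.80 |
|---|---|---|---|
| Two-sided | 0.74 | 0.805 | 30 |
| Two-sided | 0.43 | 0.374 | 86 |
| Two-sided, average of the two effects | 0.585 | 0.606 | 47 |
| One-sided | 0.74 | 0.882 | 24 |
| One-sided | 0.43 | 0.500 | 68 |

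The smallest effect detectable with 80% power at 30 per arm is 0.74 two-sided (0.736 before rounding) and 0.65 one-sided.

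**Attrition, as an assumed worst case.** The article gives no rate for this trial. In its Background, 8 of 10 participants completed treatment in the team's earlier pilot, which suggests 20% as an illustration. If 20% contributed no data at all, 30 × 0.8 = 24 per arm would remain. Two-sided power is then 0.709 at 0.74 and 0.308 at 0.43, and the detectable effect is 0.83.

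**What the planned model might add at 0.43.** The Data analysis plan specifies a hierarchical linear model with baseline depression as a covariate, and Table 1 schedules depression measures at every session. As a simple proxy, average the 9 post-baseline sessions and adjust for baseline, with an equal assumed correlation r between all measurements. The residual variance of that average is (1 + 8r)/9 − r².

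- r = 0.3: 0.378 − 0.090 = 0.288
- r = 0.5: 0.556 − 0.250 = 0.306
- r = 0.7: 0.733 − 0.490 = 0.243

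The effective d is the average effect over the sessions divided by the square root of that variance.

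- *Full effect of 0.43 from session 2 onward:* effective d = 0.80, 0.78 and 0.87; power = 0.86, 0.84 and 0.91.
- *Effect growing linearly to 0.43 at session 10:* the average effect is 0.43 × 5/9 = 0.239; effective d = 0.45, 0.43 and 0.48; power = 0.40, 0.38 and 0.45.

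Power at 0.43 therefore runs from about 0.4 to about 0.9, depending on assumptions that the article does not state.

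**The case against.** The strongest objection is that the t-test is not the planned analysis. A repeated-measures model with baseline adjustment can be much more efficient, and under a constant effect it passes 0.80 even at 0.43. This stands to the extent that 0.37 is the power of a two-sample t-test and not the power of the trial. A reader might infer that the trial cannot reach 80% power at 0.43 under any analysis, or that baseline adjustment cannot help; the documents do not support either. Nor do they support the opposite. The section claims no such gain, and an effect fully present from session 2 sits poorly with a model built on a linear time trend and a time-by-treatment interaction.

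Second, sidedness is not stated and the hypothesis is directional. One-sided, 80% power is reached from about 0.65, so it would be too strong to say that 80% is reached only at 0.74 and only without dropout. One-sided power at 0.43 is still 0.50.

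Third, the attrition figures remove participants entirely, whereas the model keeps partial records and the pilot figure concerns treatment completion, not loss from the analysis. They are a worst case and should be labelled as such.

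Fourth, the wording is loose: 30 does lie inside the 30 to 86 range, and the article does not say outright that 0.80 is attained at each effect. But a value at the bottom edge is not well inside the range.

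Finally, the article discloses that the sample is small, warns of type II error and gives a separate stage-of-development rationale. That rationale can justify 60 participants, but it cannot make the power sentence right. The warning covers only small differences, while the article itself counts 0.43 in its medium-to-large span.

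**Conclusion.** Wrong as written. Under a two-sided two-sample t-test at alpha 0.05 with complete data, 30 per arm meets the stated 80% at 0.74 (power 0.81). It falls well short at 0.43, where power is 0.37 and 86 per arm would be needed. Neither a one-sided test (0.50) nor averaging the two effects (0.61) repairs this, and nothing stated in the section does.

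The conclusion rests on reading the effects as standardised mean differences and on the section's own inputs. It concerns the sentence, not the choice of 60 participants. It does not say that the planned model will be underpowered at 0.43, which cannot be settled without assumptions the article does not give.

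**What to change.** Keep 60 participants and restate the power sentence in Sample size considerations along these lines:

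> For a two-sided two-sample t-test at alpha 0.05 with complete data, 30 per arm gives 80% power for d of about 0.74 and about 37% power for d = 0.43. As an assumed worst case in which 20% contribute no data, power is about 0.71 and 0.31 respectively, and the detectable d is about 0.83.

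If a gain from the hierarchical linear model is relied on, add the assumed correlation between measurements and the assumed trajectory of the effect, with the resulting power.

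In the Discussion, change the limitation so that the differences that may go undetected include medium effects such as the trial's own 0.43, not only small ones. A commitment to report the treatment difference with its 95% confidence interval would help readers of a non-significant result, but it is optional.

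The cost is a few sentences. Design, sample size and analysis are unchanged; the stated power becomes less favourable.

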### Data analysis plan

We will first assess equivalence of random assignment of groups, patterns of missing data, research dropout rates, and distributional properties of all measures. Hierarchical linear modeling (HLM) [68] will be used to examine within-subject change of depression (first aim) and activation and reinforcement derived from the environment (second aim) over the course of treatment. The nature of HLM analyses allows us to control for baseline scores of each measure, include multiple measurement points while accommodating missing data, examine individual change over time in outcomes, and include the average change and the individual variation around this average change. We will specify all of our HLM level-1 intercepts and slopes as random, given that we expect first session depressive symptomatology, activation, and availability of reinforcement in the environment, as well as each individual’s slope of these constructs, to differ across our participants. We will center all variables of interest around the mean of respective scores to avoid multicollinearity. Planned covariates in these analyses will include gender, recruitment method, and baseline levels of depressive symptoms, as well as the main effect of treatment condition and the linear effect of time. Inclusion of the time by treatment condition interaction will indicate the extent to which treatment differences are more or less pronounced early versus later across treatment sessions. Categorical rates of remission of MDD will be examined across treatment conditions using the Cochran-Mantel-Haenszel test, controlling for gender.To examine the correspondence between increases in activation and environmental reinforcement with depression, we will also use HLM to examine correspondence of these variables over time. These models will include the aforementioned covariates in addition to including activation and environmental reinforcement as time-varying predictors of depression, the main effect of treatment condition, the linear effect of time, and the inclusion of time by treatment condition interaction. Because of the difficulty in attributing causality between variables assessed at the same time-point, we will also conduct analyses predicting depression with environmental reinforcement and activation assessed at the previous time-point as time-varying covariates (please see Figure 1 depicting the lagged and concurrent analyses). These lagged analyses will indicate whether the predictors predict change in depression at subsequent assessments, consistent with the BATD framework that activation and environmental reinforcement are expected to increase before depression decreases.

To examine more closely the effects of treatment on attendance, we will conduct a Cox proportional hazards survival analysis predicting days to attrition. This will allow us to examine the extent to which BATD was able to increase the latency to treatment attrition. Homework completion will be assessed by dividing the total number of completed homework sessions by the total number of assigned homework sessions for each participant. We will conduct *t*-tests to examine differences in homework completion between BATD and SC.

Finally, we will conduct *t*-tests examining differences between BATD and SC in treatment satisfaction, therapeutic alliance, and perceived stigma at each session these correlates were examined.

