Following up this promising initial work, the current study is comprised of an RCT with three aims. First, we will compare the impact of BATD and a supportive counseling (SC) condition on participants’ depression throughout the course of the study. We expect that participants randomized to BATD will evidence greater reductions in depressive symptoms and a higher percentage remission of MDD relative to participants randomized to the SC condition. Second, we will compare group differences on the proposed mediators of BATD, including activation and contact with environmental reward. We hypothesize that participants assigned to the BATD condition will evidence greater increases in activation and contact with environmental reward relative to those assigned to the SC condition. We also expect that increases in activation and contact with environmental reinforcement will correspond with decreases in depression. Figure 1 is a depiction of the models tested under this aim. Third, we will examine SC and BATD group differences on key conceptually relevant variables associated with treatment retention and outcomes in Latinos, such as treatment satisfaction [41], therapeutic alliance [42], and perceived stigma [43], as these variables have been shown to affect treatment outcomes and retention in this population. In the context of the third aim, we will compare dropout rates between conditions. We expect that, relative to participants assigned to the SC condition, participants randomized to BATD will evidence higher treatment satisfaction given the heavy emphasis of BATD on putting effort into one’s recovery from depression ("poner de su parte"), a treatment expectation highly valued in this population [44,22]. Further, we hypothesize greater therapeutic alliance in the BATD condition given the collaborative approach expected to emerge between the client and the therapist in this treatment condition [45]. We also hypothesize that, as a result of the conceptualization of depression of BATD as originating from the lack of environmental reinforcement, perceived stigma levels will be lower relative to the SC condition. Finally, we expect that treatment retention will be greater for the BATD condition than for the SC condition based on previous findings suggesting this trend [39,40].

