**Figure 1 F1:**
[figure not shown]
**Representation of models that will test the correspondence between increases in activation and contact with environmental reinforcement, and decreases in depression.** Model 1 will test the simultaneous correspondence between depression with activation and environmental reinforcement. Model 2 will test if increases in activation and contact with environmental reinforcement predict depression.

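### Activation and reward enter the depression models as single undivided predictors, so the mechanism coefficients blend within-person with between-person association and do not cleanly test whether increases go with decreases

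*Protocol article*

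**What the plan says.** The last paragraph of Background sets the second-aim hypothesis: "We also expect that increases in activation and contact with environmental reinforcement will correspond with decreases in depression". The Figure 1 legend assigns the concurrent part to the first of two models: "Model 1 will test the simultaneous correspondence between depression with activation and environmental reinforcement".

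The Data analysis plan (Methods/design) gives the model:

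- Centring: "We will center all variables of interest around the mean of respective scores to avoid multicollinearity".
- Predictors: "including activation and environmental reinforcement as time-varying predictors of depression", one term each.
- Covariates: "Planned covariates in these analyses will include gender, recruitment method, and baseline levels of depressive symptoms", plus treatment condition, linear time and their interaction. No person mean of activation or reward is listed.
- Random effects: "We will specify all of our HLM level-1 intercepts and slopes as random". The reason given is that first-session levels are expected to vary, "as well as each individual’s slope of these constructs, to differ across our participants".
- Lagged model: "environmental reinforcement and activation assessed at the previous time-point as time-varying covariates", with no different centring stated.

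**The concern.** The hypothesis is about change: when a person becomes more active, that person becomes less depressed. A session score on BADS or RPI carries two kinds of information: how active the person generally is, and how far this session departs from that. If generally more active people are generally less depressed, an undivided score can show a negative coefficient even when nobody's depression moves with their own activation. The plan itself expects people to differ in their levels, so this is not a remote case.

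At stake is the mechanism claim. The abstract presents the trial as among the first to examine these mechanisms over time, and a coefficient reported as correspondence of change could partly reflect stable differences between people.

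**Working it through.** The plan states no figure on this point, so there is none to reproduce. The check has three parts.

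**1. Where the mixing comes from.** Subtracting a constant c changes only the intercept: β(x − c) = βx − βc. Raw and grand-mean-centred scores therefore give the same slope, apart from how the random effects are parameterised. Now write x_ij = (x_ij − x̄_i) + x̄_i for person i at session j. A single β forces the deviation and the person mean to share one coefficient. The missing split is the cause, not the centring constant.

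**2. Weights in closed form** (random intercept, one predictor, no covariates):

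β = w·β_within + (1 − w)·β_between, with w = W_w/(W_w + W_b)

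W_w = (T − 1)·s²_w/σ²; W_b = T·(s²_b + s²_w/T)/(σ² + T·τ²)

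T is 11 from Table 1 (sessions 1–10 and 1 month). The intraclass correlations (ICCs) are assumptions: 0.3–0.7 for the predictor, 0.1–0.7 for residual depression. Total variances are set to 1.

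- Predictor 0.7, depression 0.1: W_w = 10 × 0.3/0.9 = 3.33; W_b = (7.7 + 0.3)/(0.9 + 1.1) = 4.00; w = 3.33/7.33 = 0.46 (0.455 to three decimals).
- Predictor 0.5, depression 0.5: W_w = 10 × 0.5/0.5 = 10; W_b = (5.5 + 0.5)/(0.5 + 5.5) = 1; w = 10/11 = 0.91.
- Predictor 0.3, depression 0.7: W_w = 10 × 0.7/0.3 = 23.33; W_b = (3.3 + 0.7)/(0.3 + 7.7) = 0.5; w = 0.98.

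The within-person weight is thus 0.46–0.98 with 11 occasions. With only 4 occasions it is 0.30–0.92.

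**3. Simulation with the planned baseline covariate.** Inputs: 60 people; 11 occasions, the first used as the baseline; random intercept; time, treatment, their interaction and baseline depression as covariates; 0% or 50% early dropout (assumed, since the Discussion expects high dropout but gives no figure); two-sided 5%; 300 runs per setting. True within-person slope 0. Rejection rates, 0% / 50% dropout:

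| ICC predictor / depression | Undivided, between slope −0.3 | Undivided, between slope −0.6 | Deviation term, all four settings |
|---|---|---|---|
| 0.5 / 0.4 | 11% / 10% | 22% / 21% | 5–6% |
| 0.7 / 0.3 | 30% / 26% | 59% / 64% | 4–7% |
| 0.3 / 0.6 | 4% / 7% | 11% / 6% | 4–8% |

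Monte Carlo error at 5% is √(0.05 × 0.95/300) = 1.3 points.

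With a true within-person slope of −0.3, over the same ICCs and dropout rates:

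| Between slope | Undivided estimate | Deviation estimate |
|---|---|---|
| −0.3 | −0.26 to −0.29 | −0.29 to −0.30 |
| −0.8 | −0.30 to −0.39 | −0.30 |
| +0.3 | −0.12 to −0.28 | −0.30 |

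**Effect of adding baseline activation.** In one setting (ICCs 0.5/0.5, between-person correlation −0.5, no within-person effect, no dropout, 300 runs), the undivided term rejected in 19% of runs with no baseline covariate, 14% with baseline depression, and 8% with baseline activation added. The split gave 4%. In two further assumed settings (120 runs each), adding baseline activation cut rejection from 12.5% to 7% and from 37.5% to 11%.

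**Random slopes.** A run with random intercept and slope (150 replicates, ICCs 0.4–0.6, between-person correlation −0.5 to −0.6) gave 19–24% undivided against 4–9% for the deviation. Adjustment for baseline depression is not documented for it, so it shows only that random slopes do not remove the mixing.

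**The case against.** The strongest reply is that the sentence never says grand mean. The article condenses a fuller protocol, and the same section describes the models as examining individual change, so person-mean centring may have been intended. It is true that the text does not exclude it. But the article does state the rule, its reason and the terms. Collinearity is not a reason for separating levels, and a rule for all variables cannot mean person means for gender or recruitment method. If person means were intended for BADS and RPI, the sentence is still ambiguous on the choice that decides what the coefficient means.

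A second reply is that the damage may be small. Random intercepts and up to 11 occasions pull the estimate towards the within-person slope, and baseline depression removes some of the rest. The section also says that these models allow control for the starting value of each measure. Baseline activation is not in the covariate list for the depression models, but if it were added the inflation would shrink a good deal. This stands as a limit on size. It does not remove the blend.

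A third reply is that the plan itself doubts causal reading of same-time associations and adds lagged models. That is fair, but the lagged predictors are undivided too.

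A reader might infer that the concurrent model cannot test the hypothesis at all, or that a positive result would be an artefact. The documents do not support this. With both slopes at −0.3 the undivided estimate was close to the truth and power was about 1.

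**Conclusion.** The point holds in a limited form. On the natural grand-mean reading, which is an inference, the activation and reward coefficients blend within-person with between-person association, and the concurrent model does not cleanly test the second-aim hypothesis. The lagged model shares the structure.

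The size cannot be fixed from the document. Under the assumed ICCs, between-person slopes and dropout, with zero within-person effect and baseline depression adjusted for, the false-positive rate runs from about nominal (4–11%) through 10–22% to 26–64%. It is lower with baseline activation as a covariate. No single figure should be quoted as the bias.

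The comparisons between arms on depression, activation and reward do not use these time-varying terms and are unaffected. This is a change worth making to part of the second aim, not a threat to the trial's main comparison.

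**What to change.** State which mean is used. For BADS (total and activation subscale) and RPI in the depression models, replace the single term with two: the person's own mean over sessions (level 2) and the session deviation from that mean (level 1). Name the deviation coefficient as the test of the hypothesis. Grand-mean centring can stay for level-2 covariates.

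Apply the same separation in the lagged model, and note there that a person mean over all sessions includes sessions later than the outcome being predicted.

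The cost is one revised sentence and two derived variables per predictor, with no new data. The interval for the within-person coefficient becomes slightly wider, and person means are imprecise for participants who leave after few sessions, which matters given the dropout that the Discussion foresees.
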